### Outcomes

#### Primary outcome 1: Stated intention to undertake a context specific behaviour

Behavioural intentions are commonly used as proxy measures for subsequent behaviours in contexts where valid measurement of subsequent behaviours is unfeasible [50]. Aligned with this, participants will be asked their intention to undertake a context specific behaviour after viewing the intervention. Responses will be scaled using a 5-point Likert Scale (‘much less inclined’, ‘less inclined’, ‘about the same’, ‘more inclined’ and ‘much more inclined’).

#### Primary outcome 2: Stated intention to encourage family or friends to undertake a context specific behaviour

Participants will be asked their intention to encourage family or friends to undertake a context specific behaviour after viewing the intervention. Responses will be scaled using a 5-point Likert Scale (‘much less inclined’, ‘less inclined’, ‘about the same’, ‘more inclined’ and ‘much more inclined’). Levels of trust in family or friends has been shown to be similar to other sources regarding COVID-19 information.(23) This level of trust, combined with the high levels of opportunity for conversations to take place between family and friends regarding public health measures makes this arguably an important outcome to influence.

#### Secondary outcome 1: Stated feelings of inclusion or representation in the developed video and how they correlate to level of agreement of the message in the video

For this outcome, we are aiming to understand how represented the participants feel in each of the intervention videos, and what impact this has on the level of agreement to the message in the video. Immediately after viewing each video, participants will be asked to indicate their level of agreement using a 5-point Likert Scale (’strongly disagree’, ’disagree’, neither agree nor disagree’, ’agree’, ’strongly agree’).

Once all interventions have been viewed, participants will then be asked if being strongly represented in a health message videos impacts the extent to which they are more inclined to agree with the message in a video public health message using a 5-point Likert Scale (’strongly disagree’, ’disagree’, neither agree nor disagree’, ’agree’, ’strongly agree’).

### Procedure

Vulnerable subgroup populations will be recruited from partner organisations listed in Table 2. An advertisement via email, in person or via the partner organisation social media pages will be used, explaining the basic details of the project and what is required. A link to the explanatory statement and survey will also be included in this advertisement and participants will be able to complete the survey independently in their own time, with assistance from a family member or carer, or with assistance from a member of the corresponding partner organisation team if completing the survey on site. All information (explanatory statements, survey questions and video information) will be captioned, translated, interpreted or adapted accordingly to the communication profiles of the different vulnerable subgroup populations. This includes Auslan for the deaf and hard of hearing group, and Dari and Sinhalese for the refugee and asylum-seeker group. The general community group will be recruited online using social media platforms (i.e. Facebook and Twitter).

**Table 2 pone.0280865.t002:** Partner organisations related to each subgroup population.

Vulnerable Subgroup	Partner Organisation
**People living with a disability and their carers**	Able Australia, Wallara and Yooralla
**Aged care workers**	Donwood Community Aged Care Services
**Refugee and asylum seekers**	enliven
**Deaf, hard of hearing people**	Expression Australia and Able Australia
**Aboriginal and Torres Strait Islander peoples**	Peninsula Health
**Street-based sex workers**	St Kilda Gatehouse
**General Australian community**	Not applicable.

Randomisation will occur automatically via the inbuilt randomisation function on the Qualtrics data collection platform (Qualtrics, Provo, UT, USA). Therefore, random allocation will be fully concealed from participants and investigators involved in recruitment and data collection.

### Study timeline

Participants will be able to access the relevant survey (to their subgroup) leading to either Trial 1 then Trial 3 (combined) or Trial 2 then Trial 3 (combined) independently or with assistance from the corresponding Partner Organisation. By following the link to the corresponding survey for each subgroup population, participants will have access to the explanatory statement including inclusion and exclusion criteria. From there, participants can choose to participate and confirm they adhere to the inclusion criteria. The data collection and survey builder software Qualtrics (Qualtrics, Provo, UT, USA) will automatically, randomly allocate participants into one of four potential combinations of allocation using a Latin Square approach for both Trial 1 and Trial 2, (minimising study level order effects), and will again randomly assign to one of two possible combinations for Trial 3. Data will be extracted for analysis purposes with no follow-up period required. Refer to Fig 1 for an overview of the study timeline.

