### Participants and setting

This study will include a sample of the general Australian community as well as six subgroup population groups. Trial 1 will only include participants from the six vulnerable population groups, Trial 2 will only include participants from the general Australian community, and Trial 3 will include participants from all six vulnerable subgroups as well as the general Australian community.

These communities can be argued to be vulnerable to infection, transmission and experiencing negative health and other outcomes during the COVID-19 pandemic on the basis of their pre-existing lower health equity due to socioeconomic factors, increased risk of COVID-19 exposure, cultural factors, need for support for decision making due to intellectual or cognitive changes and/or augmentative or alternative communication methods or challenges experienced in communicating (Table 1) [10, 39, 40].

**Table 1 pone.0280865.t001:** Project population subgroups and their associated COVID-19 risk factors & communication challenges.

COVID-19 risk factors & communication challenges	Population subgroup					
	Aboriginal & Torres Strait Islander peoples	People living with disability & their carers	Refugee & asylum seekers	Deaf, hard of hearing people	Aged care workers	Street-based sex workers
Higher exposure risk		**Applicable** [12, 41] due to personal care tasks			**Applicable** due to work	**Applicable** [6, 7] due to work
Higher rates of health conditions & need for health services	**Applicable** [12, 41]	**Applicable** [12, 41]	**Applicable** [42]			**Applicable** [7]
Difficulty accessing health care	**Applicable** [41]		**Applicable** [42]			**Applicable** [6, 7]
Higher rates of limited English proficiency			**Applicable**		**Applicable**	
Lower rates of digital literacy and access to the Internet or Internet-enabled devices		**Applicable** [43, 44]				
Limited accessible COVID-19 information		**Applicable** [12]		**Applicable** [45]		
Loss of educational support and access		**Applicable**	**Applicable**	**Applicable** [46]		
Different cultural understandings of illness	**Applicable**		**Applicable**			
Lower SES	**Applicable** [47]	**Applicable** [12]	**Applicable** [42]			**Applicable** [7]
Higher rates of contract, casual or precarious work		**Applicable** [48]			**Applicable**	**Applicable** [6, 7]

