### Interventions

#### Trial 1 (vulnerable groups only)

This trial will involve factorial allocation of two intervention factors each with two levels (2x2 factorial) across four context areas. These factors are:

Factor 1: Who is providing the message (general practitioner versus community representative).Factor 2: How is the message being delivered (animation versus talking head).

Both general practitioners and community representatives will be selected due to their high level of perceived trust in vulnerable subgroup communities, making them a viable potential deliverer of messages in real life. However, from a public health messaging perspective, a general practitioner can be used to develop a message that may potentially impact a range of vulnerable groups quickly in a pandemic context, whereas it takes more time and greater cost to produce messages delivered by specific vulnerable community representatives as each vulnerable community requires its own representative and own message to be produced. The talking head versus animation intervention approaches were selected as both are commonly used, yet are competing visual imagery approaches in public health messaging.

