#### Trial 3 (all participants)

Trial 3 will include two intervention arms across two different context areas related to COVID-19 health. The two arms of the study will be:

Conversational training approach provided by a general practitioner (talking head).Direct information provision provided by a general practitioner (talking head).

The arms of study differ by the language, content and tone. The conversational training approach provides a health message in a peer-to-peer fashion that is expressed in a relaxed conversational tone. The direct information provision arm, provides a health message that is direct and didactic in style, and does not provide suggested statements that people could say in a discussion with another person on this topic.

The two context areas will be:

Encouraging people who have workers coming to visit them at home to ask them if they are vaccinated or not.Encouraging people to avoid sharing food, utensils and other items at gatherings.

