### Analysis

The comparisons we will undertake across the three trials will be:

#### Trial 1

Main effect of who is providing the message (General Practitioner versus community representative).Main effect of visual stimulus (talking head versus animation).Interaction effect between these two main effects.Simple effects if interaction effect is significant.

#### Trial 2

General practitioner talking head visual stimulus delivered health message versus animated general practitioner visual stimulus delivered health message.Politician visual stimulus delivered health message versus general practitioner talking head visual stimulus delivered health message.Written delivery of health message (control) versus all other intervention types (general practitioner talking head, general practitioner animation and politician delivered health message).

#### Trial 3

The effectiveness of health information provision delivered through a conversational training approach by a general practitioner versus through a direct information provision approach by a general practitioner.

Comparisons will not be made between context areas as part of the primary analysis. However, we will investigate interaction effects of the different intervention comparisons across the different context areas and population subgroups so that we can understand whether certain interventions work better in certain contexts and populations.

Linear mixed model analyses will be used treating the intervention levels as fixed factors and participants as random factors. Context will be ignored when investigating intervention main effects as it will be balanced across the different intervention levels.

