### Sample size

The repeated-measures, latin square design creates an analysis paradigm comparable to a paired-sample comparison of proportions. The least statistical power generated through the helix design arises when there is a simple contrast between two levels of an intervention within a singular vulnerable group category. Power analysis for this context can be approximated by a power analysis conventionally performed for McNemar’s Test, though we will be using linear mixed models for our analyses. A sample size of 36 participants per subgroup will provide 80% to detect a difference in proportions of respondents being “more inclined” or “much more inclined” with a primary outcome statement from 0.2 to 0.4. This assumes a correlation between the outcome proportions of (0.61) and a two-tailed alpha of 0.05. We aim to recruit 40 participants per vulnerable subgroup to allow for ~10% partial completion of the full survey. The study is conducted in a single session so there is no further allowance for loss to follow-up (this is irrelevant in our context). No maximum sample size will be set for the community sample given our online recruitment approach and short time-frame for data collection negating the need to cease the trial “early” due to important findings being identified.

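### Trial 3 always comes last, so its result is conditional on four earlier messages and its community-versus-vulnerable interaction cannot be separated from which trial came first

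*Protocol article*

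**What the plan says.** All references are to the Protocol article.

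- **Order.** Study timeline offers one survey per group, "leading to either Trial 1 then Trial 3 (combined) or Trial 2 then Trial 3 (combined) independently". Sample size adds: "The study is conducted in a single session".
- **Who takes which route.** Participants and setting: "Trial 1 will only include participants from the six vulnerable population groups, Trial 2 will only include participants from the general Australian community", whereas "Trial 3 will include participants from all six vulnerable subgroups as well as the general Australian community".
- **Messages before Trial 3.** Trial 1 has "two intervention factors each with two levels (2x2 factorial) across four context areas", and each participant works through a full combination column (legend to Fig 2). That makes two general practitioner (GP) and two community-representative messages. In Trial 2 each participant gets all four arms: GP talking head, GP animation, politician and written text.
- **Trial 3.** Both arms use a GP talking head. One is the conversational approach and the other is "Direct information provision provided by a general practitioner (talking head"). Each participant receives both arms, one per context area, in one of two randomised combinations.
- **Order protection.** Study timeline describes allocation to four combinations "using a Latin Square approach for both Trial 1 and Trial 2, (minimising study level order effects"). Trial 3's allocation is a separate randomisation.
- **Analysis.** Beyond the main comparisons, "we will investigate interaction effects of the different intervention comparisons across the different context areas and population subgroups". The Trial 2 section uses population subgrouping to mean general community versus vulnerable groups.

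Neither Analysis nor Limitations mentions the fixed position of Trial 3 or the different trial that precedes it.

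**The concern.** Trial 3 is the only one of the three trials that spans all seven groups. By its registered title it asks which strategy works for vulnerable and community populations alike, and the Objective is framed for all Australians. Two things limit what it can say.

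First, nobody is measured on Trial 3 without four preceding COVID-19 messages. If earlier messages alter how people respond to a conversational or a direct GP video, the estimated difference belongs to that primed state.

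Second, the priming differs between the community and the vulnerable groups, and it does so for every participant. If the arm effect differs between them, the planned interaction cannot show whether the population or the preceding trial is responsible. A decision to use one style for the community and another for vulnerable groups could rest on that interaction.

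**Working it through.** **1. The plan's own figure.** The only sample-size calculation is for paired proportions of 0.2 and 0.4, correlation 0.61, two-sided alpha 0.05 and 80% power, giving 36 per subgroup. These inputs imply discordance pd = 0.2009 with difference 0.2. Then n = (1.96·√pd + 0.84·√(pd − 0.2²))² / 0.2² = 36.98, so 37 against the stated 36; power at 36 is 0.789. Inflation gives 36/(1 − 0.10) = 40, as stated. The figure is sound to rounding. The point does not depend on it, but steps 5 and 6 use it.

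**2. Exposure before Trial 3, by route.**

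| | Vulnerable (Trial 1 first) | Community (Trial 2 first) |
|---|---|---|
| GP talking head | 1 | 1 |
| GP animation | 1 | 1 |
| Community representative | 2 | 0 |
| Politician | 0 | 1 |
| Written | 0 | 1 |
| Total | 4 | 4 |

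**3. Aliasing.** Being vulnerable and having Trial 1 first correlate at 1.0. A Trial 3 fixed-effects matrix with 7 group terms and 7 group-by-arm terms has rank 14. Adding preceding trial and preceding trial by arm gives 16 columns, and the rank stays at 14. Seven groups give 6 interaction degrees of freedom. The 5 among the six vulnerable groups are not aliased, because all six have the same preceding trial. The remaining one, community versus vulnerable, is aliased completely.

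**4. What each estimate contains.** Let θ be the arm effect (conversational minus direct) without earlier messages, and λ the change in that effect caused by earlier messages. Subscripts V and C denote the vulnerable and community routes.

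- Vulnerable estimate: θV + λV. Community estimate: θC + λC.
- Interaction: (θC − θV) + (λC − λV).
- Carry-over that shifts both arms equally cancels within the person, so λ = 0. In simulation with a true effect of 0.200 this returned 0.200 and an interaction of about 0.
- Illustration only: take θV = θC = 0.20, λV = −0.15 (assumed), λC = 0 and equal numbers on both routes. The interaction is 0.20 − 0.05 = 0.15 with no population difference, and the pooled effect is (0.05 + 0.20)/2 = 0.125. The simulation gave 0.153 and 0.124.

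**5. What the existing randomisation can check.** Contexts come in a set order and intervention levels follow a Latin square, so the Trial 1/2 combination (C1–C4) determines the last message seen. With 6 × 36 = 216 completers there are 216/4 = 54 per combination on the vulnerable route. Under the plan's assumptions the within-person difference has SD √(0.2009 − 0.04) = 0.401. Comparing two combinations has standard error 0.401 × √(2/54) = 0.077, so 80% power needs a change in arm effect of about 2.80 × 0.077 = 0.22. That is as large as the planned effect, so only gross carry-over would show.

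**6. Cost of relying on a Trial-3-first half.** If block order were randomised 1:1, about 40/2 = 20 per vulnerable subgroup would take Trial 3 first. Power for the plan's within-subgroup contrast is then Φ((0.2·√20 − 1.96·√0.2009)/0.401) = Φ(0.04), about 52%.

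**The case against.** The strongest reply is that a fixed order does not bias Trial 3. Each participant gets both arms in randomised combinations, and both arms follow the same four messages. That stands. A reader might infer that the contrast carries a carry-over bias. If earlier messages change the arm difference, that is effect modification and limits generalisability; it does not undermine the randomised comparison.

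A reader might also infer that the direct arm suffers from repetition while the conversational arm gains from novelty. The protocol does not support this. It never describes delivery in Trials 1 and 2 as direct or didactic, and one of the two earlier GP messages is an animation. The helix design separates exposures by context, and Trial 3's two contexts do not occur in Trials 1 and 2. This makes carry-over less likely but does not exclude it.

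Nor does the protocol clearly claim to have balanced Trial 3's position. The remark on order effects attaches to the Latin squares of Trials 1 and 2.

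Finally, population is not randomised. Groups also differ in recruitment channel, language, assistance and setting, so the community-versus-vulnerable interaction is observational in any case, and the article lists it outside the named Trial 3 comparison. This lowers the weight of the point without removing it: the alias with preceding trial is total, is created by the design, and is not acknowledged.

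**Conclusion.** The point holds in a limited form. The conversational-versus-direct contrast is internally valid but applies to people who have just seen four COVID-19 messages. The community-versus-vulnerable part of the Trial 3 interaction (1 of 6 degrees of freedom) is completely aliased with preceding exposure and cannot be attributed to population. It would go too far to call the whole population interaction confounded, since contrasts among the six vulnerable groups do not depend on which trial came first.

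This rests on the text of Study timeline, Participants and setting, and Sample size. The figures are not shown, but the text fixes the order. The size of any carry-over is unknown; the 0.15 above is an assumption and not evidence that carry-over exists. The issue is one of interpretation and reporting, and it changes what Trial 3 may conclude.

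**What to change.** 1. In the Trial 3 model, add the randomised Trial 1/2 combination (C1–C4) and its interaction with arm, separately for each route, as a carry-over check. State its limited power. It tests whether the particular sequence, and so the last message seen, matters; it cannot show the effect of having seen no messages, and it does not break the alias.
2. State the main Trial 3 conclusion as conditional on prior exposure. Report the community-versus-vulnerable interaction as the joint effect of population and preceding trial, and keep the subgroup interaction for contrasts among the vulnerable groups. Add this to Limitations.
3. Make clear in Study timeline that the order-effect wording covers only order within Trials 1 and 2.

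These need text and a few model terms, and no new data.

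Optional, as a trade-off: randomise block order in Qualtrics, with an order term and an order-by-intervention interaction in the models of all three trials. This would break the alias and make carry-over estimable. It needs an ethics and registry amendment, and half the Trial 1/2 responses would then follow two GP talking-head videos, which could affect the GP contrasts in those trials. The interaction should not be based on the Trial-3-first half alone, given about 20 per vulnerable subgroup.

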### Data management

Information relating to the participation in the trial will not be available to any persons outside the study team. De-identified aggregate data from this research will be shared publicly only in peer reviewed journals, conferences and reports back to the participants and partner organisations (where appropriate). De-identified results data can be made available upon request to study investigators.

### Analysis

The comparisons we will undertake across the three trials will be:

#### Trial 1

Main effect of who is providing the message (General Practitioner versus community representative).Main effect of visual stimulus (talking head versus animation).Interaction effect between these two main effects.Simple effects if interaction effect is significant.

#### Trial 2

General practitioner talking head visual stimulus delivered health message versus animated general practitioner visual stimulus delivered health message.Politician visual stimulus delivered health message versus general practitioner talking head visual stimulus delivered health message.Written delivery of health message (control) versus all other intervention types (general practitioner talking head, general practitioner animation and politician delivered health message).

#### Trial 3

The effectiveness of health information provision delivered through a conversational training approach by a general practitioner versus through a direct information provision approach by a general practitioner.

Comparisons will not be made between context areas as part of the primary analysis. However, we will investigate interaction effects of the different intervention comparisons across the different context areas and population subgroups so that we can understand whether certain interventions work better in certain contexts and populations.

Linear mixed model analyses will be used treating the intervention levels as fixed factors and participants as random factors. Context will be ignored when investigating intervention main effects as it will be balanced across the different intervention levels.

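### The simple two-level contrast is not the least-powered planned test: interactions of the same size within or between subgroups have less power, and this matters if Trial 1's simple effects are made conditional within a subgroup

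*Protocol article*

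**What the plan says.** The Analysis section of the protocol article lists four items for Trial 1: the main effect of who gives the message, the main effect of visual stimulus, their interaction, and "Simple effects if interaction effect is significant". It then adds, for all three trials, that interactions of the intervention comparisons with context area and with population subgroup will be examined.

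The Sample size section states: "The least statistical power generated through the helix design arises when there is a simple contrast between two levels of an intervention". The rest of that sentence places the contrast inside one vulnerable group. On that basis, "A sample size of 36 participants per subgroup will provide 80% to detect a difference in proportions", counting people who are at least more inclined, "with a primary outcome statement from 0.2 to 0.4". The other inputs are in the next sentence: "This assumes a correlation between the outcome proportions of (0.61) and a two-tailed alpha of 0.05". The method is the power calculation "conventionally performed for McNemar’s Test, though we will be using linear mixed models for our analyses". The recruitment target is 40 per vulnerable subgroup. No interaction size, and no power for any interaction, is given.

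**The concern.** The least-power sentence carries no exception. A reader will take it that every planned comparison has at least 80% power for a difference of 0.20, including the interactions meant to show which messages work in which populations and contexts. If that is untrue, a non-significant interaction may be over-read as evidence that effects are equal. This bears on the use the Discussion has in mind: whether one general practitioner message, or one animation, could replace group-specific media.

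The condition on simple effects adds to this. If the 2×2 analysis is run within a subgroup, the type of contrast used for sizing is examined only after a less powerful test succeeds. The 80% then no longer describes the chance of finding it.

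**Working it through.** **Inputs.** From Sample size: 36 per subgroup, proportions 0.2 and 0.4, correlation 0.61, two-sided alpha 0.05, power 80%. From Interventions and Design: Trial 1 is a 2×2 factorial in which each participant sees all four cells, one per context. From Study timeline: Trial 3 has two allocation combinations. From Participants and setting: six vulnerable groups.

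**1. The plan's own figure.** McNemar normal approximation:
- Both positive: p11 = 0.2×0.4 + 0.61×√(0.16×0.24) = 0.1995.
- Discordant: 0.4 − 0.1995 = 0.2005 and 0.2 − 0.1995 = 0.0005, so pd = 0.2009 and d = 0.20.
- n = [1.96√pd + 0.842√(pd − d²)]²/d² = 36.98, that is 37. Power at 36 is 78.9%.

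The stated 36 is reproduced to within one participant.

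**2. Contrast variances in Trial 1.** Let v be the within-participant error variance of one cell (equal variances and correlations assumed, no extra context variance). Per participant:
- main effect, the mean of two simple effects: v
- simple effect, one cell minus another: 2v
- interaction, one simple effect minus the other: 4v

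The interaction's standard error is √(4v/2v) = √2 times that of a simple effect.

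**3. Power within one subgroup of 36.** Eighty per cent power corresponds to a standardised effect of 1.96 + 0.84 = 2.80. For an interaction of the same 0.20, this becomes 2.80/√2 = 1.98, giving 51%. The ratio is 51/80 = 0.64. Restoring 80% takes 2×36 = 72 per subgroup.

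With binary variances instead (0.24 in one cell, 0.16 in three, all correlations 0.61), the interaction has 61% against 85–89% for the simple contrast, a ratio of about 0.7.

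**4. Dependence on the pattern**, one subgroup, first simple effect 0.20:

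| Second simple effect | Interaction size | Interaction power |
|---|---|---|
| 0.10 | 0.10 | 17% |
| 0 | 0.20 | 51% |
| −0.10 | 0.30 | 84% |
| −0.20 (full crossover) | 0.40 | 98% |

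**5. The condition, applied within a subgroup**, with effects 0.20 and zero. The interaction and the simple effect are correlated 1/√2, and both are significant in about 49% of trials. The main effect, halved to 0.10, also has 51% power. In simulation, neither interaction nor main effect is significant in about 24% of trials, and simple effects estimated only after a significant interaction are on average about 20% too large.

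**6. Pooled over six groups**, n = 6×36 = 216, same pattern: 2.80×√6/√2 = 4.85, giving 99.8%. For effects of 0.20 and 0.10 the pooled interaction power is 68%.

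**7. Other planned interactions.**
- Difference of 0.20 in effect between two subgroups of 36: twice the variance of one subgroup's contrast, so 1.98 again and 51%.
- Trial 3 arm by context within a subgroup. With two combinations of 18, this contrast compares participants' summed responses between the combinations. Its variance is 4s²(1 + 0.61)/18. With s² from 0.16 to 0.24 the standard error is 0.239 to 0.293. A 0.20 interaction then gives 0.84 to 0.68 standard errors and power of 13% to 10%.

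**The case against.** Examining simple effects after a significant interaction is the conventional factorial sequence, and it limits the number of contrasts. That stands: the rule is not an error in itself.

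The rule is listed as a Trial 1 comparison. Trial 1 covers all six vulnerable groups, and the Design section describes a pooled analysis. At that level the interaction test is almost certain to succeed under the 0.20-and-zero pattern, and selection bias is negligible. This also stands, and it confines the practical harm to within-subgroup use, which the Analysis section does not explicitly prescribe.

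The sizing sentence covers all three trials and may be meant to rank only the two-level contrasts. Among those it is reasonable, since main effects have smaller variance at equal effect. The sentence is nevertheless stated for the whole design, while the Analysis section plans interactions, so it is wrong as written.

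A reader might infer two stronger things. One is that the interaction test has half the chance of success of the contrast that depends on it. It does not: 51% is an absolute power, and half of 80% would be 40%. The other is that the plan will usually miss simple effects. The documents give no interaction size and do not say that the condition is applied by subgroup. When effects run in opposite directions, the interaction can have more power than the simple contrast (84% and 98% above).

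**Conclusion.** The least-power statement is incorrect and should be corrected. For an equal difference of 0.20, the who-by-visual interaction within a subgroup has about 51% power against 80%, a between-subgroup difference in effect about 51%, and the Trial 3 arm-by-context interaction within a subgroup about 10–13%.

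The condition on simple effects is a secondary matter. For an interaction of 0.20 it has consequences only where the 2×2 analysis is run within a subgroup. There, the 80% falls to about 49% for both tests succeeding if one simple effect is 0.20 and the other zero. Other patterns give interaction power from 17% to 98%.

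These figures rest on a normal approximation, equal variances and correlations across cells, no added context variance, and complete data on 36 participants per subgroup. The effect patterns are assumptions, because the protocol states none.

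**What to change.** In Sample size, restrict the least-power and 80% statements to two-level intervention contrasts. Add that interaction tests of the same size, within or between subgroups, have lower power and are exploratory.

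In Analysis for Trial 1, report the four cell means and the simple effects (who within each visual format, visual format within each messenger) with 95% confidence intervals whether or not the interaction is significant. Give the interaction estimate with its own interval. State that a non-significant interaction within a subgroup will not be read as evidence that the simple effects are equal.

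This changes wording and reporting only; recruitment, materials and randomisation are untouched. The small downside is more contrasts in the tables, which should be labelled as secondary.
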